### Study Sample

The study sample will consist of 220 women diagnosed with cervical, vaginal or endometrial cancer and who will receive primary or postoperative EBRT+BT (BT boost by intra-uterine and/or vaginal brachytherapy) or postoperative EBRT alone. This also includes curative treatment with EBRT+BT for local relapse after previous surgery. Participants are recruited in specialized GC treatment centres in the Netherlands. Women are eligible for study participation if they (1) are 18 years or older, (2) receive treatment with RT for GC as specified above and (3) wish to retain their sexual activity in the short- or long term. Women are excluded from study participation if they (1) are unavailable for follow-up, (2) have insufficient command of the Dutch language or (3) have a major affective disorder, psychotic disorder, substance abuse disorder or posttraumatic stress disorder resulting from abuse in the pelvic floor area and/or genitals. To ensure appropriate treatment of these women with more severe psychological and/or psychiatric problems, they are referred to a specialized psychologist/sexologist connected to the own GC centre or are advised to consult their general practitioner to be referred to a specialized psychologist/sexologist or psychiatrist.

### Recruitment and randomization

The treating radiation oncologists screen potential participants with regard to the inclusion and exclusion criteria. Eligible women are informed about the background, rationale and specifics of the study protocol. Women who want to participate in the study provide written informed consent and complete a paper-and-pencil baseline questionnaire before randomization. After inclusion, participants are assigned a unique study identifier by the local data manager, which will be filled out on all questionnaires and used in the data files. Inclusion and randomization take place before the completion of RT. Participants are randomized to either the intervention- or the optimal CAU control group (1:1), and within each centre stratified by type of radiotherapy (EBRT+BT versus EBRT only) and having a partner (yes/no). The randomization is block stratified with varying block sizes, and is performed by the local data manager, using a secured web-based data-management system.

### Study groups

One month after completion of RT, women in both study groups receive an information booklet. The information booklets, which contain specific information to improve knowledge and coping strategies regarding sexual rehabilitation after either EBRT+BT or EBRT only, are based on the booklet developed in the pilot study [32]. The booklets are provided in both a printed and online version. Women in both study groups who received EBRT+BT are given a dilator set and are advised to start vaginal dilation for 1 to 3 min, 2 to 3 times a week around 4 weeks after RT when the vagina is sufficiently healed [11, 18].

#### Training of the nurses

The intervention is conducted by oncology nurses who have completed a 50-hour study-specific training in sexology and simple cognitive behavioural interventions and the treatment protocol itself. The nurses are supervised by an experienced sexologist once per month. Every six months, the oncology nurses and their supervisors attend an additional day of training that is focused on a specific theme that is relevant for the study (i.e. vaginal stenosis and dilator use, emotional reactions after loss of participants due to cancer recurrence, and the partner relationship).

#### Intervention group: the nurse-led sexual rehabilitation intervention

The intervention consists of four one-hour face-to-face sessions at 1, 3, 6, and 12 months post-RT. These sessions are planned synchronously with women’s radiation oncologist follow-up visits. An additional session is scheduled for women who received EBRT+BT at 2 months, during which potential barriers and problems with dilator use are discussed. Furthermore, if preferred, an extra follow-up session/telephone consultation of 30 min can be scheduled between 6 and 12 months after RT. If a woman is in a relationship, the partner is invited to accompany her in the sessions.

The sexual rehabilitation intervention consists of 11 modules. A description of the content of the modules is provided in Table 1. The modules include topics such as education regarding the specific cancer diagnosis and treatment, education on the importance of regular use of vaginal dilators (if applicable), discussing potential experienced barriers to dilator use (if applicable) and lubricant use, fear of penetration with dilators (if applicable) and fear of resuming sexual activity after cancer, promoting couples’ mutual coping and support processes and addressing sexual and body image concerns. The content of the intervention is a personalized programme tailored to the participant-specific psychological, relational and somatic factors. During a session, the oncology nurse selects the specific module(s) that fits the woman’s (and her partner’s) needs. The decision tree for module selection is provided in Fig. 2.

**Table 1 Tab1:** Description of the sexual rehabilitation intervention modules

**Module 1: Brief sexual history**	This module describes how the nurse can question the patient in-depth about sexual problems on various domains of sexual functioning, including sexual interest/arousal, orgasm, pain and sexual satisfaction. It also covers psycho-education about sexuality and the sexual response curve [33] and provides information about frequently occurring sexual problems and solutions.
**Module 2: Pain during intercourse**	This module includes practical guidelines that the nurse can provide regarding pain during intercourse after radiotherapy-, with referrals to module 3, 4, 6 and 7, and explains how to provide psycho-education about the circular model of dyspareunia [34], which is based on a cognitive behavioural framework.
**Module 3: Vaginal dryness and health**	This module provides the nurse with instructions on how to give advice with regard to treatment of vaginal dryness, pain or irritation. It also includes information regarding vaginal health, such as the use of vaginal creams, avoidance of scratching in response to irritated skin or avoidance of washing with soap.
**Module 4: Alternatives for intercourse**	The exercise in this module helps the woman and her partner (if available) to explore and discuss non-penetrative alternatives for sexual intercourse.
**Module 5: The partner and possible sexual problems**	This module can be consulted by the nurse when partners experience temporary sexual problems, such as erectile dysfunction during intercourse. The module also includes a reference to module 1.
**Module 6: Gradual exposure towards sexual intercourse**	The aim of the steps in this module, which are based on a cognitive behavioural gradual exposure therapy for Genito-Pelvic/Penetration Disorder [29], is to learn the woman and her partner how to re-engage in sexual intercourse. The steps include: touching of the vaginal opening with the erect penis without penetration, stepwise vaginal insertion of the erect penis without moving, and vaginal insertion of the erect penis with moving.
**Module 7: Pelvic floor exercise**	This module includes several pelvic floor relaxation exercises for women who experience tension in the pelvic floor muscles.
**Module 8: Difficulties with dilator use at home**	This module is suitable for women who experience problems with dilator use and who already practiced under supervision of a nurse (see module 9) or for women who do not want to practice under supervision. This module provides the nurse with instructions on how to give specific advice on how to overcome experienced difficulties, after first exploring the problems during dilator use (e.g. pain/discharge, loss of blood or difficulties with inserting the dilator).
**Module 9: Using dilators under supervision at the outpatient clinic**	This module focuses on women who experience fear with regard to dilator use or who experience difficulties when using vaginal dilators, due to for example tension of the pelvic floor. The nurse-led session is based on therapist-aided exposure therapy for Genito-Pelvic/Penetration Disorder [29]. The goal is to reduce fear of dilator use by using a stepwise exposure session in which the woman - who performs the vaginal dilation by herself - is facilitated by the nurse. During the session, tips are given with regard to a correct and more comfortable use of the dilators. Furthermore, the nurse helps to evaluate and articulate any unhelpful cognitions about what could (or could not) occur during dilator use. In these instances, the exposure is used as a behavioural experiment, to test the tenability of these cognitions. The module also includes advice on how to handle problems that might occur during practicing at home.
**Module 10: Exploring and resolving ambivalence with regard to dilator use**	The aim of the exercise in this module is to motivate the woman for dilator use, by acknowledging, exploring and resolving ambivalent feelings towards dilator use by motivational interviewing technique [35]. By exploring pros and cons of both dilator use and no dilator use, the woman can be supported in making an informed choice about dilator use. If she decides to use dilators, problems with dilator use are discussed in more detail and how to overcome them. If a woman decides not to use dilators, tampons covered in petroleum jelly (Vaseline) are recommended and guidelines on how to use these are provided to the woman (see module 11).
**Module 11: Petroleum jelly (Vaseline) tampons**	This module follows module 10, when a woman decides not to use dilators. The module covers guidelines on how to use tampons covered in petroleum jelly (Vaseline).

**Fig. 2 Fig2:**
[figure not shown]
Decision Tree intervention modules. BT = Brachytherapy; EBRT = External Beam Radiotherapy; MI = Motivational Interviewing [35]; Module 1 = Brief sexual history; Module 2 = Pain during intercourse; Module 3 = Vaginal dryness and health; Module 4 = Alternatives for intercourse; Module 5 = The partner and possible sexual problems; Module 6 = Gradual exposure towards sexual intercourse; Module 7 = Pelvic floor exercise; Module 8 = Difficulties with dilator use at home; Module 9 = Using dilators under supervision at the outpatient clinic; Module 10 = Exploring and resolving ambivalence with regard to dilator use; Module 11 = Petroleum jelly (Vaseline) tampon

All sessions will be audio-taped allowing a direct check on the oncology nurses’ adherence and competency. A random check of 30% of audio-taped sessions on adherence of the treatment protocol will be performed by two independent researchers. Furthermore, these audio-taped treatment sessions will be used for supervision purposes.

#### Control group: Optimal Care As Usual

All participating women are offered an information session, information booklet and a dilator set (if applicable) post-RT free of charge. Hereby, we optimized the CAU control group in our current study. Although CAU cannot be completely standardized, as the procedure is dependent on the local standard practice, it will not involve a structured, tailored nurse-led sexual rehabilitation intervention.

### Data collection

Participants are requested to complete questionnaires prior to randomization (T1, baseline) and at 1, 3, 6, and 12 months post-RT (T2, T3, T4 and T5, respectively, see Fig. 1). The T1 questionnaire is completed on paper. The T2-T5 study questionnaires can be completed either online (a link is sent by email) or on paper, depending on the preference of the participant. An online reminder is sent to participants who do not complete and return the questionnaire within one week. If a participant does not complete the questionnaire in the week following the reminder, she is contacted by telephone. Vaginal symptoms, assessed by standardized clinical examination during a physical examination, are synchronously collected at the timepoints of the T1-T5 questionnaires through Case Report Forms (CRFs) and medical records. For women who withdraw early from study participation, data collected until the moment of withdrawal will be available for analysis.

### Measures

#### Sociodemographic and clinical data

Sociodemographic data are obtained via the T1 questionnaire and include age, relational status, living situation, having children, education, and work status. Clinical data are collected from medical records and through CRFs at T1 and include date of gynaecological cancer diagnosis, type of gynaecological cancer (cervical/endometrial/vaginal) and characteristics (histological type, Fédération Internationale de Gynécologie et d’Obstétrique (FIGO) stadium, lymph node metastases), treatment(s) received (surgery, chemotherapy, type of radiotherapy, hypothermia), height and weight, and smoking. In addition, World Health Organisation (WHO) performance status, menopausal status and medication use (including hormonal replacement therapy) are collected from medical records and through CRFs at T1-T5.

#### Outcome measures

Detailed descriptions of the outcome measures are provided in Table 2. The primary outcome measure is a standardized patient-reported outcome measure (PROM) assessing sexual functioning (Female Sexual Function Index (FSFI) [36]). The secondary outcome measures include PROMs assessing vaginal symptoms and body image concerns (European Organization for Research and Treatment of Cancer Quality of Life Questionnaire-Gynaecological Cancer Module (EORTC QLQ-CX24) [37]), fear of coital and non-coital sexual activity (Fear of Sexuality Questionnaire (FSQ) [38]), sexual distress (Female Sexual Distress Scale (FSDS) [39]), treatment-related distress (Impact of Event Scale (IES) [40]), generic health-related quality of life (European Organization for Research and Treatment of Cancer Quality of Life Questionnaire Core 30 (EORTC QLQ-C30) [41]), urological and gastrointestinal symptoms and sexual interest (European Organization for Research and Treatment of Cancer Quality of Life Questionnaire-Endometrial Cancer Module (EORTC QLQ-EN24) [42]), psychological distress (Hospital Anxiety and Depression Scale (HADS) [43]), and relationship satisfaction (Maudsley Marital Questionnaire (MMQ) [44]). To minimize respondent burden, the T1-questionnaire includes only the FSFI [36] and the FSDS [39].

**Table 2 Tab2:** Study outcome measures and corresponding questionnaires

Variable	Questionnaire	Details

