#### Other study parameters

In addition to treatment- and patient characteristics, treatment credibility and expectancy for improvement will be assessed using the 4-item Credibility and Expectancy Questionnaire (CEQ) [47]. These parameters will be measured at T3. Additionally, at T2-T5 all women will be requested to report the use of any counselling or therapy in the course of their rehabilitation period. Furthermore, the type (face-to-face or by telephone) and the duration of the session, and modules used during the session are documented by the oncology nurses in CRFs. Finally, for each participant, the date of the completion of study participation and the reason for ending study participation are registered in web-based CRFs.

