### Statistical analysis

T-tests or appropriate non-parametric statistics for independent samples will be used to evaluate the comparability of the intervention and control group at baseline in terms of sociodemographic and clinical characteristics. If, despite the stratified randomization procedure, the groups are not comparable on one or more background variables, those variables will be employed routinely as covariates in subsequent analyses.

Questionnaire scores will be calculated according to published scoring algorithms. Differences in changes in the primary outcome measure and secondary outcome measures between groups (intervention vs. control group) over time (T1-T5) will be evaluated using multilevel models and are based on an intention-to-treat approach. Effect sizes will be calculated using standard statistical procedures.

Furthermore, multilevel models will be used to investigate if improvement in sexual functioning in the intervention group is moderated by treatment/cancer characteristics and patient characteristics or mediated by e.g. sexual symptoms and vaginal symptoms or frequency of dilator use. Cost-effectiveness will be analysed using net benefit analysis, with multiple imputation to account for missing data.

Per protocol analyses will also be carried out (as a secondary analysis), comparing women who meet minimal compliance levels with the intervention with the control group. We will use correlation analyses to examine the relationship between degree of intervention adherence and intervention effect.

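### Differences in change over T1–T5 are planned for the secondary outcomes, but seven of the eight secondary questionnaires named in the text have no T1 value

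*Protocol article*

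**What the plan says.** The Statistical analysis section sets one analysis for all outcomes: "Differences in changes in the primary outcome measure and secondary outcome measures between groups (intervention vs. control group) over time (T1-T5) will be evaluated". The models are to be multilevel and the principle is intention to treat. The section makes no exception for any secondary measure.

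Data collection fixes the time points: "Participants are requested to complete questionnaires prior to randomization (T1, baseline) and at 1, 3, 6, and 12 months post-RT". Outcome measures then limits what is asked at the first of them: "To minimize respondent burden, the T1-questionnaire includes only the FSFI [36] and the FSDS [39". That section names eight secondary patient-reported questionnaires: QLQ-CX24, FSQ, FSDS, IES, QLQ-C30, QLQ-EN24, HADS and MMQ.

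One further secondary outcome is measured at T1 outside the questionnaire. The clinically examined vaginal symptoms "are synchronously collected at the timepoints of the T1-T5 questionnaires through Case Report Forms (CRFs) and medical records".

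On the intervention, the protocol states: "The intervention consists of four one-hour face-to-face sessions at 1, 3, 6, and 12 months post-RT". The visits are meant to coincide with the radiation oncologist's own follow-up appointments. The first session and T2 therefore share the nominal time of one month after radiotherapy. The text does not say which comes first.

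**The concern.** The stated analysis window and the stated collection schedule cannot both hold for the seven questionnaires without T1 data. No other baseline, and no T2–T5 window, is given for them. These scales carry body image, fear of sexual activity, treatment-related and psychological distress, health-related quality of life and relationship satisfaction. Of the secondary outcomes listed in the abstract, only sexual distress lies outside them.

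The practical risk is a quiet substitution. A group-by-time model run on these scales will fit without complaint, with T2 as its first time point, and its interaction terms can then be reported as differences in change. That is a different estimand from the one planned, because T2 comes after randomisation and at the nominal start of the intervention. If the window stays open, the reference point and the main contrast for most secondary outcomes could also be settled after the data are seen.

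**Working it through.** **1. The plan's own figure.** The sample size concerns the FSFI only. For 0.5 SD, two-sided 5% and 80% power, the two-sample t-test needs 63.8, so 64 per group (power 80.1% at 64). With 40% attrition, 64 / 0.6 = 106.7, so 107 per group and 2 × 107 = 214, rounded up to 220. The figures reproduce. The FSFI is measured at T1, so nothing below touches them.

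**2. Planned window against available data.**

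| Outcome | Planned window | Measured at T1? |
|---|---|---|
| FSFI (primary) | T1–T5 | yes |
| FSDS | T1–T5 | yes |
| Clinical vaginal examination | T1–T5 | yes, by CRF and medical record |
| QLQ-C30, QLQ-CX24, QLQ-EN24, FSQ, HADS, IES, MMQ | T1–T5 | no |

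Of the 8 secondary questionnaires named in Outcome measures, 8 − 1 = 7 have no T1 value. Table 2 adds the EQ-5D-5L and the CEQ, which makes 10 − 1 = 9 of 10. The count of seven is the fair one for this point:
- The CEQ rates treatment credibility, and Other study parameters says of it: "These parameters will be measured at T3". No T1 value is to be expected.
- The dilator-use items concern use after radiotherapy, so the same applies.
- The EQ-5D-5L also lacks a baseline, but that bears on the QALY calculation.

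**3. What a T2 reference would estimate.** Let d_k be the true difference between arms in mean score at T_k.
- Change from T1 to 12 months: d_5 − d_1. T1 precedes randomisation, so d_1 = 0 in expectation and the contrast equals d_5.
- Change from T2 to 12 months: d_5 − d_2. This equals d_5 only if d_2 = 0. T2 follows randomisation and shares its nominal time with the first session, so d_2 = 0 is not guaranteed.
- Direct comparison at 12 months: d_5. It needs no baseline.

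The amount removed by a T2 reference is d_2. The document gives no value for it, and does not say how many women complete T2 after the first session. No figure can be put on the loss.

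**4. Precision without a same-scale baseline.** Adjusting a single follow-up score for its baseline multiplies the variance of the arm comparison by 1 − ρ², where ρ is the baseline–follow-up correlation. The document gives no ρ, so the range is an assumption.

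| Assumed ρ | 1 − ρ² | Standard error without baseline, relative to with: 1/√(1 − ρ²) |
|---|---|---|
| 0.3 | 0.91 | 1.05 |
| 0.5 | 0.75 | 1.15 |
| 0.7 | 0.51 | 1.40 |

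This loss follows from the short T1 form, not from how the analysis is worded. Adjustment for T1 FSFI and FSDS may recover part of it.

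**The case against.** The strongest reply is that little is broken. A multilevel model uses whatever time points exist, so the seven scales can be modelled over T2–T5, and randomisation keeps comparisons at follow-up valid without a baseline. The hypothesis about improvement from baseline to 12 months covers only sexual functioning and dilator compliance. The short T1 form is a disclosed choice with a stated reason. Analysis windows per outcome are commonly set in the SAP, which is not at hand. And the article nowhere proposes T2 as a baseline.

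Most of this stands. A reader might infer that the secondary questionnaires cannot be analysed at all. The document does not support that: only change from T1, adjustment for the same scale at baseline and a check of baseline balance on it are lost. It is also right that a T2 reference is something an analyst might fall back on, not something the plan states.

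The SAP argument does not remove the point. The article does not leave the window open; it names T1–T5 for primary and secondary measures alike, and its own schedule contradicts that for seven questionnaires. An SAP that repeats the sentence inherits the error, and one that departs from it leaves the published plan wrong.

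**Conclusion.** The point holds as an internal contradiction. Change from T1 cannot be estimated for 7 of the 8 secondary questionnaires named in Outcome measures. This rests only on reading the two sections together. The primary FSFI analysis, the FSDS, the clinical vaginal examination and the sample size are unaffected.

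A reader might go further and infer that these secondary results will be biased towards zero by a definite amount. The document does not support that. The bias arises only if T2 is used as the reference, and only if an early effect already exists at T2. The text does not establish whether T2 precedes or follows the first session (the content of Fig. 1 is not shown), and it gives no early effect for any of these scales. The 0.5 SD in the sample size section is the FSFI design effect and is no yardstick for them. What can be said is the direction: if the early and later effects share a sign, change from T2 understates the later one.

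**What to change.** In the Statistical analysis section:
- Restrict change over T1–T5 to the FSFI, the FSDS and the clinical vaginal examination.
- For QLQ-C30, QLQ-CX24, QLQ-EN24, FSQ, HADS, IES and MMQ, estimate the difference between arms at each of T2–T5 in a multilevel model, with 12 months as the main contrast. Adjust for the randomisation factors (centre, type of radiotherapy, partner) and for T1 FSFI and FSDS.
- Treat T2 as an outcome, not as a baseline or covariate. Using it as a covariate only where it precedes the first session would not work, because control women have no first session and the rule would depend on arm.
- Do not describe the results for these seven scales as change from baseline.

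The cost is a few lines of text, best settled before the arms are compared. No change to visits or questionnaire scheduling is needed; altering T2 timing while the trial is recruiting would put two T2 regimes into one dataset. The remaining downside is lower precision on these scales than a same-scale baseline would have given, which rewording cannot recover.
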